### **3.1.2.2 Exclusion Criteria**

1. Pregnancy: Patients with pregnancy/perinatal ICD diagnosis codes in EHR.

2. Malignancy

3. End-stage kidney disease: maintenance kidney replacement or kidney transplantation by ICD codes, or  $\text{eGFR} < 15 \text{ mL/min/1.73m}^2$

### **3.1.3 High-risk Patients for CKD**

#### **3.1.3.1 Inclusion Criteria**

1. Age  $\geq 18$  years

2. No established diagnosis of CKD

3. Presence of at least one of the following risk factors:

(1) Type 2 diabetes mellitus (T2DM) (ICD-coded)

(2) Hypertension (ICD-coded)

(3) Cardiovascular disease (ICD-coded)

(4) Obesity: body mass index (BMI)  $\geq 28.0 \text{ kg/m}^2$  per Chinese expert consensus, or relevant ICD-10 codes.

(5) History of AKI/AKD: meeting either KDIGO SCr criteria or a clinical diagnosis, as detailed in **Table 3**

(6) Kidney stones (ICD-coded)

(7) Family history of kidney disease

(8) Advanced age ( $>60$  years)

#### **3.1.3.2 Exclusion Criteria**

Identical to the exclusion criteria specified in section 3.1.2.2 for the CKD population.

### **3.2 Study Interventions**

This study employs a multi-faceted intervention strategy, comprising a structured training program for PCPs and the implementation of a CDSS within the EHR infrastructure of community health services in Beijing Xicheng District, with administrative support from the Beijing Municipal Government and Xicheng District Health Commission.

---

### 3.2.1 CDSS

The CDSS will be developed using a Plan-Do-Check-Act framework and will be integrated into the existing EHR system. In the Plan phase, semi-structured interviews with PCPs will be conducted to identify user needs. The Do phase will involve a multidisciplinary team (including nephrologists, technical experts, and PCP representatives) in designing an initial prototype. A pilot study at an independent primary care center will then be conducted as the Check phase, during which the system will be iteratively refined. Finally, the Act phase will consist of evaluating the system's effectiveness and implementation feasibility through the main clinical trial described above. The CDSS is designed to provide non-intrusive, real-time clinical decision support during patient encounters. The key functionalities deployed in the intervention arm include:

1. Automated case identification & risk stratification: The system automatically identifies patients with or at risk of CKD through structured diagnostic codes and laboratory data.

2. Renal referral for patients without prior diagnosis of CKD

- (1) Rapid decline in renal function meeting the AKD criteria (**Table 3**).

- (2) Presence of refractory hypertension: defined as blood pressure (BP) >140/90 mmHg while prescribed  $\geq 3$  antihypertensive medications, or being prescribed  $\geq 4$  classes of antihypertensive medications.

- (3) Persistently proteinuria, hematuria or eGFR <60 mL/min/1.73m^2 (two consecutive abnormal results obtained  $\geq 90$  days apart)

3. Automated CKD staging (stages 1-5)

4. Structured management protocols for diagnosed CKD patients:

- (1) Stage-specific monitoring of renal function (e.g., eGFR, UACR every 3 month).

- (2) Complication management alerts for identification, evaluation and management targets based on thresholds defined as follows: hypertension (BP >130/80 with proteinuria or >140/90 without), CKD-mineral and bone disorder (CKD-MBD) (corrected Ca2+ <2.2 mmol/L; PO4 >1.61 mmol/L), hyperkalemia (K+ >5.5 mmol/L), metabolic acidosis (pH <7.25 or HCO3 <22 mmol/L), anemia (Hb <120 g/L [Male] / <110 g/L [Female]), and dyslipidemia (LDL-C >1.8 mmol/L).

5. Renal referral for CKD patients presenting with following indications:

- (1) Advanced CKD (stage 4-5)

- (2) With any of the following complications: rapid eGFR decline meeting AKD criteria; persistent hematuria ( $\geq 20$  RBCs/HPF,  $\geq 80$  RBCs/ $\mu$ L, or occult blood  $\geq 2+$ ) on consecutive tests; refractory hypertension; hypoproteinemia (serum albumin <35g/L); CKD-MBD; severe anemia (Hb <100 g/L); significant proteinuria (UACR  $\geq 300$  mg/g

---

or UTP  $\geq 1.0$  g/day, or  $\geq 0.5$  g/day in diabetics); or persistent hyperkalemia ( $K^+ > 5.5$  mmol/L after initial treatment).

6. Treatment recommendations for CKD patients:

(1) SGLT2is are recommend as first-line treatment for patients with T2DM and an eGFR  $\geq 30$  mL/min/1.73 m^2.

(2) GLP-1 RAs are introduced for patients with T2DM and suboptimal glycemic control on metformin and SGLT2i, with eGFR  $\geq 15$  mL/min/1.73 m^2.

(3) RAASi are recommended for patients with proteinuria and/or hypertension, contingent upon the following criteria: eGFR  $\geq 30$  mL/min/1.73 m^2 (within the past 6 months), serum  $K^+ < 5.5$  mmol/L (within the past 6 months), and absence of bilateral renal artery stenosis.

(4) Dosing for all relevant medications should be adjusted according to renal function, as specified in **Table 4**.

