| Field search for AKI/AKD            | "acute renal failure", "acute kidney injury", "acute kidney disease", "acute renal failure"                                                                                                                                                                                                                                                                                                                                                                                                                                                                                                                                                                                                                                                                                                                                                                                                                              |

468 AKI, acute kidney injury; AKD, acute kidney disease; SCr, serum creatinine; eGFR,  
 469 estimated glomerular filtration rate.

470 **Table 4. Safety reminder for hypoglycemic drugs.**

| Drug Class                       | Common medications | Medication Reminders from Chinese Diabetic Nephrology Clinical Prevention and Treatment Guidelines                                                                                                                                                                                                                                                                                                                                                                                                 | Medication reminders                                                  |
|----------------------------------|--------------------|----------------------------------------------------------------------------------------------------------------------------------------------------------------------------------------------------------------------------------------------------------------------------------------------------------------------------------------------------------------------------------------------------------------------------------------------------------------------------------------------------|-----------------------------------------------------------------------|

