|                  | Lixisenatide  |                                                                        |                                                          |
| SGLT2 inhibitors | Dapagliflozin | ○ eGFR <60: not recommended                                            | eGFR < 60: contraindication                              |
|                  | Empagliflozin | ○ eGFR <45: contraindication                                           | eGFR < 45: contraindication                              |
|                  | Canagliflozin | ○ eGFR 45-60: maximal dose of 100mg/day
○ eGFR <45: not recommended | eGFR 45-60: dose reduction
eGFR <45: contraindication |

471 eGFR, estimated glomerular filtration rate; GLP-1, glucagon-like peptide-1; ESRD,  
472 end-stage renal disease; SGLT2, sodium-glucose cotransporter 2  
473

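### The CDSS recommends SGLT2 inhibitors from eGFR 30 upwards, but Table 4 contraindicates all three listed agents at eGFR 30–44

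*Protocol*

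**What the plan says.** Protocol Section 3.2.1 lists the functions of the CDSS, and item 6 gives its treatment recommendations for CKD patients. Item 6(1) reads "SGLT2is are recommend as first-line treatment for patients with T2DM and an eGFR" of 30 mL/min/1.73 m² or more. Item 6(4) then refers to Table 4: "Dosing for all relevant medications should be adjusted according to renal function, as specified in" that table.

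Table 4 is titled "Safety reminder for hypoglycemic drugs". It has a guideline column and a column of medication reminders, and lists three SGLT2 inhibitors:

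- Dapagliflozin: the guideline column has "eGFR <60: not recommended" and the reminder has "eGFR < 60: contraindication".
- Empagliflozin: both columns give a contraindication below 45.
- Canagliflozin: the guideline column caps the dose at eGFR 45–60 and has "eGFR <45: not recommended". The reminder has "eGFR 45-60: dose reduction", followed by "eGFR <45: contraindication".

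**The concern.** The recommendation and the reminders belong to the same decision-support module and cover the same drugs in the same patients, yet their eGFR limits differ. Over part of the range, a physician who follows item 6(1) prescribes a drug that Table 4 says must not be given.

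Two things are at stake. The first is clarity of prescribing advice. The users are primary care physicians, and the protocol's Background reports that only 24.9% of those in Beijing were aware of fundamental CKD concepts, so they may be poorly placed to settle the conflict themselves. The second is interpretation of secondary outcome 2 (Section 3.3.2), which reports SGLT2 inhibitor prescribing among CKD patients without an eGFR restriction. Patients at eGFR 30–44 count towards it, but the text does not show whether the system encouraged or discouraged prescribing in them.

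**Working it through.** No power, alpha or sample size figure bears on this point, so the check is a comparison of ranges.

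**Inputs** (eGFR in mL/min/1.73 m²)

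- Recommended range, Section 3.2.1 item 6(1): eGFR ≥30, with type 2 diabetes.
- Contraindicated range, Table 4 reminder column: dapagliflozin <60, empagliflozin <45, canagliflozin <45. No other SGLT2 inhibitor is listed.

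**Overlap per agent** = recommended range ∩ contraindicated range

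- Dapagliflozin: ≥30 and <60, giving 30–59.
- Empagliflozin: ≥30 and <45, giving 30–44.
- Canagliflozin: ≥30 and <45, giving 30–44.

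**Agents both recommended and contraindicated, by eGFR band**

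| eGFR | Dapagliflozin | Empagliflozin | Canagliflozin | In conflict |
|---|---|---|---|---|
| 30–44 | conflict | conflict | conflict | 3 of 3 |
| 45–59 | conflict | no restriction | reduced dose | 1 of 3 |
| ≥60 | none | none | none | 0 of 3 |

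**Distance between the limits**

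- Empagliflozin and canagliflozin: 45 − 30 = 15 units.
- Dapagliflozin: 60 − 30 = 30 units.

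**Is one column simply mistyped?** This is unlikely. The guideline column uses the same cut-offs as the reminder column for all three agents (60, 45, 45). Its wording is milder for two of them (not recommended, rather than contraindicated), but item 6(1) agrees with neither column.

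**Are such patients in the trial?** Yes. Under Section 3.1.2.1, two eGFR values below 60 at least 90 days apart qualify a patient. Under Section 3.1.2.2, the only eGFR limit that excludes is <15. Patients at 30–44 lie between the two.

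**Does item 6(4) settle it?** No. It concerns dose adjustment, and a contraindication is not a dose. If Table 4 is taken to override, item 6(1) has no listed drug to offer at 30–44 and its limit of 30 is too low for every listed agent. If item 6(1) is taken to override, the Table 4 reminders are wrong over that range.

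**The case against.** The best defence is that the two rules work in sequence. Item 6(1) recommends at class level, and Table 4 then checks the individual agent against renal function. On that reading the reminder stops the prescription and the clash errs towards caution. The text permits this reading but does not state it. Even so, no listed agent survives the check at 30–44, so the lower limit in item 6(1) would still be wrong.

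Table 4 heads its drug column as common medications, so it does not claim to be exhaustive. That is fair: the count of 3 of 3 describes listed agents and does not show that no SGLT2 inhibitor could be used.

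The outcome argument is limited. The definition of secondary outcome 2 and the intention-to-treat comparison do not depend on what the system advised at 30–44. What remains is a difficulty of interpretation, in a subgroup of unknown size.

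Safeguards exist. Nephrologists help to design the system, a pilot refines it (Section 3.2.1), and CDSS quality indicators are verified weekly (Section 4). These may catch the conflict in operation, but none of them says which rule governs, and the protocol still carries both.

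**Conclusion.** The contradiction is real and should be fixed. As written, all three listed SGLT2 inhibitors are both recommended and contraindicated at eGFR 30–44, and dapagliflozin also at 45–59, in patients who are eligible for the trial. The conclusion rests only on the stated limits in item 6(1) and Table 4, whose SGLT2 inhibitor rows are complete in the text.

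Three things cannot be determined from the protocol: which limit was intended, which was programmed, and how many patients with type 2 diabetes have an eGFR of 30–44. The size of any effect on the SGLT2 inhibitor outcome is therefore unknown. The primary outcomes, the sample size and the validity of the randomised comparison are unaffected.

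**What to change.** With clinical sign-off, set one eGFR range for each SGLT2 inhibitor and use it in both item 6(1) and the Table 4 reminder. Suitable wording for item 6(1) would be: *An SGLT2 inhibitor is recommended first-line for CKD patients with type 2 diabetes only at an eGFR where at least one listed agent is not contraindicated in Table 4, and the recommendation names only those agents.* This works whichever limits are chosen:

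- If the Table 4 limits stand, item 6(1) starts at 45 (empagliflozin, and canagliflozin at reduced dose), and dapagliflozin is named only from 60.
- If 30 stands, the Table 4 reminders must be changed to match.

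Which limit is clinically right is not a question this review can answer. If the system is already live, the sponsor should document which rule was programmed and the date of any correction.

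The cost is the clinical sign-off, a short edit to item 6(1) and the SGLT2 inhibitor rows of Table 4, and an update to the CDSS rules. For a live system there is one small downside: a dated rule change within the intervention period, to be noted when the SGLT2 inhibitor outcome is reported. Outcome definitions, sample size and analysis model stay as they are.

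Two separate checks fit the same edit. Item 6(2) introduces GLP-1 receptor agonists from eGFR 15 in patients on metformin and an SGLT2 inhibitor, whereas Table 4 contraindicates metformin below 45 and exenatide below 30. For acarbose below 25, the reminder (reduce the dose) is less strict than the guideline entry beside it (contraindicated).

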### **3.2.2 Training Program**

With administrative support from the Beijing Municipal Government and Xicheng District Health Commission, we will conduct a structured training series to enhance CKD management capabilities. The initiative will begin with an on-site mobilization symposium, which presents the policy framework for the CKD quality improvement initiative, reviews epidemiological data on the CKD burden in Xicheng District, and emphasizes evidence-based management strategies. Participants of the symposium include key district health administrators, directors of primary care centers, and designated physician representatives across the district.

Following randomization, certified nephrologists will conduct standardized on-site training sessions at each center. These sessions will focus on clinically actionable CKD management strategies and include dedicated Q&A opportunities for PCPs. The curriculums will cover stage-appropriate monitoring intervals, evidence-based pharmacotherapy, nephrology referral criteria, and comorbidity management. At intervention centers, technical staffs will provide concurrent training to PCPs on the operation and workflow integration of the CDSS.

## **3.3 Study Outcomes**

### **3.3.1 Main Outcomes**

1. Hospitalization rates for kidney-related (acute kidney injury, progression of kidney disease, or requiring dialysis) or cardiovascular events including myocardial infarction, stroke, heart failure, or cardiovascular procedures) among CKD patients.

2. Hospitalization rates for kidney-related events in patients at high-risk for CKD

Data sources for main outcomes: Electronic medical record systems of community medical institutions and Beijing medical insurance claims database.

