#### **2.2.2 Secondary Objectives**

##### **Process Measures:**

1. To assess the effect of the CDSS on the underdiagnosis of CKD, as measured by the rate of appropriate ICD-coded documentation in patient records.
2. To examine the change in the utilization rates of renoprotective medications (RAASi and sodium-dependent glucose transporters 2 inhibitor [SGLT2i]) among CKD patients.
3. To evaluate the impact of the CDSS on the screening rate for CKD (SCr and/or urine protein testing) among patients at high risk for CKD.
4. To determine the effect of the CDSS on the referral rate of CKD patients who meet guideline-based criteria for nephrology consultation.

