### **3.5.1 Data Collection and Management**

Prospective data collection will be conducted via the Xicheng District Health Commission data platform linked to the CDSS application server. Following community-developed CDISC-CRF standards, EHR and LIS data will be automatically extracted to generate electronic case report forms (eCRF). After privacy-preserving de-identification, data were synchronized daily (T+1) via a dedicated medical network to the Joint Laboratory to create the research dataset. The PostgreSQL-based research database includes structured domains for patient visits, diagnoses, prescriptions, clinical notes, vital signs, and laboratory reports, with standardized coding applied to diagnoses, medications, and laboratory data to enhance research usability.

The study endpoint—hospitalization rates for kidney-related or cardiovascular events among CKD patients—will be assessed by linking with the Beijing Municipal Inpatient Medical Insurance Database. This database provides comprehensive and auditable hospitalization records for Beijing-insured patients admitted to tertiary hospitals, including demographics, treatments, clinical diagnoses (ICD-10 coded), costs, and department information.

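### Kidney admissions, above all in the high-risk endpoint, can be detected differently by arm, because an allowed event source is the community record that the CDSS alters

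*Protocol*

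**What the plan says.** Section 3.3.1 defines two main outcomes. In CKD patients it is "Hospitalization rates for kidney-related (acute kidney injury, progression of kidney disease, or requiring dialysis) or cardiovascular events including myocardial infarction, stroke, heart failure, or cardiovascular"; the last component listed is cardiovascular procedures. In high-risk patients it is "Hospitalization rates for kidney-related events in patients at high-risk for CKD", with nothing further in that item on what counts as kidney-related. One source line covers both: "Electronic medical record systems of community medical institutions and Beijing medical insurance claims database".

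Section 3.5.1 describes linkage to the municipal inpatient insurance database, but only for the endpoint in CKD patients. Section 3 likewise attaches the linkage to the composite and the economic analysis. According to section 3.5.1 the database holds "comprehensive and auditable hospitalization records for Beijing-insured patients admitted to tertiary hospitals", including "clinical diagnoses (ICD-10 coded), costs, and department information".

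Section 3.2.1 lists what the CDSS does in the intervention arm. For case finding: "The system automatically identifies patients with or at risk of CKD through structured diagnostic codes and laboratory data". A further function is "Renal referral for patients without prior diagnosis of CKD", and another prompts referral of patients with known CKD. Section 2.2.2 makes more CKD coding, more creatinine and urine testing, and referral into process objectives; the last reads "To determine the effect of the CDSS on the referral rate of CKD patients who meet guideline-based criteria for nephrology consultation".

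Section 3.4.5 says that outcome assessors and statisticians are blinded, and that physicians and patients are not.

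**The concern.** A kidney admission enters the endpoint only after someone has tested, referred, admitted and coded the patient. The CDSS is designed to act on the first two steps and on community coding, in one arm. Table 3 defines acute kidney disease mainly by change between creatinine or eGFR results, so more frequent testing gives more chances to meet the definition without any change in disease. If events may also be read from the community record, the intervention changes the instrument that measures its own effect.

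At stake is how the second main outcome can be read. A null or adverse result there could mean that the CDSS does not help, or that it finds more of what was already present. As the sources are now written, the trial could not tell these apart. The composite is exposed to a lesser degree, through its kidney components.

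**Working it through.** **1. The source statements side by side.** Section 3.3.1: community record plus insurance claims, for both outcomes. Section 3.5.1: inpatient insurance linkage, for the CKD endpoint. The high-risk endpoint therefore has no described linkage, and its only mention of sources includes the community record. This is a stated rule, not a detail left open.

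**2. Reproducing the planned power (section 3.6.1).** Inputs: 35.0 per 100 person-years, 20% reduction, 36 months, 30 centres (15 per arm), ICC 0.02, alpha 0.05 (taken as two-sided), 3,240 patients, stated power 90%.

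- Patients per centre: 3,240 / 30 = 108; per arm: 1,620.
- Design effect: 1 + (108 − 1) × 0.02 = 3.14.
- Events per patient over three years: 3 × 0.35 = 1.05 in control; 1.05 × 0.80 = 0.84 under intervention.
- Standard error of the difference: √[(1.05 + 0.84) × 3.14 / 1,620] = 0.0605.
- Difference / standard error: 0.21 / 0.0605 = 3.47. Power from the noncentral t with 28 df: 91.7%.

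This is the variant nearest the stated 90%. Binary, one-year and person-year design-effect variants give 49% to 77%. Under the variant used here exactly 90% needs 2,670 patients, so 3,240 itself is not recovered.

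**3. Effect of extra detection.** Assume a true rate ratio of 0.80 for every component. Let s be the kidney share of control-arm events and d the factor by which better detection multiplies recorded kidney admissions in the intervention arm. The protocol gives neither value. Then

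observed rate ratio = 0.80 × [(1 − s) + s × d].

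*High-risk endpoint (s = 1):* d = 1.10 gives 0.80 × 1.10 = 0.88; d = 1.25 gives 1.00; d = 1.50 gives 1.20. No rate or sample size is stated for this endpoint, so its power cannot be computed.

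*CKD composite,* with power as in step 2:

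| Kidney share s | d = 1.10: ratio, power | d = 1.25: ratio, power | d that cancels the effect |
|---|---|---|---|
| 0.2 | 0.816, 87% | 0.84, 76% | 2.25 |
| 0.3 | 0.824, 83% | 0.86, 64% | 1.83 |
| 0.5 | 0.84, 76% | 0.90, 37% | 1.50 |

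Example: s = 0.5, d = 1.25 gives 0.80 × (0.5 + 0.625) = 0.90. The last column is 1 + 0.25/s. Applying d to all kidney events is a simplification, since dialysis is much less sensitive to detection.

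**The case against.** A reader might infer that both main outcomes as a whole rest on kidney coding and nephrology contact, or that ascertainment is bound to differ by arm. The protocol supports neither. Myocardial infarction, stroke, heart failure and cardiovascular procedures do not need a kidney code or a nephrologist. Differential detection is made possible, not shown.

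Several safeguards also count. Hospitals, not CDSS users, assign inpatient codes, so the insurance data are reached only indirectly, through referral and admission. For the composite, section 3.5.1 already points to that database, and the research database it describes lists no hospitalisation domain. Cohorts are fixed from a screening year before the intervention (section 3.1.1), so later coding does not move the denominators. Both arms are trained on referral criteria (section 3.2.2), which narrows the contrast. All of this stands and limits the point. Blinded assessment does not answer it, because the difference arises before any assessor sees a record.

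Two further arguments carry some weight. In a pragmatic trial, admissions that follow a prompted referral are arguably part of the real effect of the CDSS. That holds for cost, but not for a reading of the endpoint as less disease. And extra detection works against the intervention, so it would not create a false benefit. It can, however, hide a true benefit or suggest harm: with no true effect, d = 1.25 would give a ratio of 1.25 in the high-risk endpoint.

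Finally, principal-diagnosis rules and supportive analyses may stand in a statistical analysis plan that is not shown. Their absence is not the finding. The finding is the source rule that section 3.3.1 does state.

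**Conclusion.** The point holds for the high-risk endpoint and for the acute kidney injury and progression components of the CKD composite. Section 3.3.1 admits as a source, for both main outcomes, the record that the intervention changes in one arm, and section 3.5.1 does not settle the matter for high-risk patients.

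The size is unknown. Under the stated assumptions, 25% more recorded kidney admissions cancels a true 20% reduction in the high-risk endpoint. For the composite the same 25% lowers power from about 92% to 76%, 64% or 37% at kidney shares of 0.2, 0.3 or 0.5. It would be tempting to say that the composite effect could be wiped out, but that needs 50% to 125% more recorded kidney admissions across those shares, an extreme case.

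The power figures rest on one formula that comes close to the plan's 90%, and on the plan's use of an all-cause rate as the control rate of a cause-specific endpoint.

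**What to change.** In sections 3.3.1 and 3.5.1, state that both main outcomes are ascertained in both arms from the inpatient insurance database only, classified by principal discharge diagnosis. Pre-specify all-cause hospitalisation as a supportive analysis: it does not depend on cause coding and is the quantity that the 35.0 planning rate describes. Report the kidney and cardiovascular components of the composite separately.

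Do not add a sensitivity analysis that leaves out admissions after a nephrology referral. It would condition on a post-randomisation event that the CDSS is meant to raise, would remove more events from the intervention arm, genuine ones included, and so would favour the intervention.

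The cost is wording and one further analysis of linked data, with these limits:

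- Events recorded only in the community record, or only as secondary diagnoses, are no longer counted.
- The database is described as covering tertiary hospitals, so admissions that referral moves into those hospitals remain a limitation to be stated.
- All-cause hospitalisation still includes planned admissions after referral.
- Beijing medical insurance is an inclusion criterion for the CKD cohort (section 3.1.2.1) but is not listed for the high-risk cohort (section 3.1.3.1). The high-risk analysis would have to be confined to patients who can be linked, identified from baseline data in both arms.
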